## 3. Discussion

Using an integration of cognitive psychology, atmospheric sciences, clinical experimental medicine, and clinical biochemistry, this project aims to assess the comparative impact of source-specific aerosols on physiological and cognitive functioning. The methodology involves repeated testing pre and post exposure to controlled levels of pollutants, enabling the identification of acute changes in functioning and the detection of peripheral markers of neuroinflammation and neuronal injury.

We initially aimed for 45 participants; however, various recruitment challenges emerged during the study, such as the extended study duration, time-intensive visits, and the eligibility of those in the specific cohort of participants required. Despite efforts to alleviate the burden on participants through protocol reviews and an extensive recruitment drive involving over 45 Patient and Public Involvement and Engagement (PPIE) interactions, it became apparent that recruiting 45 participants was not feasible.

Upon reassessment, the study team adjusted the target to a smaller sample size of 15, assuming a similar dropout rate (33%). This adjustment was made to still maintain sufficient data for reasonable statistical power. Despite this adaptation, we acknowledge that the reduction in statistical power increases the likelihood of not detecting a true effect, leading to a higher risk of committing a Type II error due to wider confidence intervals. Detecting small effects is also challenging due to queries associated with using a shorter exposure time and concentrations relative to previous studies. Similarly, a smaller sample size is more susceptible to random fluctuations, which are anticipated in cognitive functioning. However, the repeated-measures design and control of participant activities during data collection aim to reduce this as a confounding variable.

We believe that, despite the increased risk of errors, the study is worthwhile with this smaller sample size, especially considering the feasibility of recruiting clinically healthy participants over the age of 50 with a family history of dementia. Furthermore, the identification of statistically significant results, showing that different pollution exposures result in different cognitive endpoints, has the potential to inform and refine policy. Indeed, hazard ranking of common air pollutants for the emerging health risk of dementia will be compelling to government, policymakers, and regulators, as well as the medical community and the public, facilitated by public health agencies and other key stakeholders.

This study aims to demonstrate that our methodology can discriminate between the cognitive impairment effects of several major representative sources of air pollution. Future research will be able to build on the results of this study by introducing further parameter space, including but not limited to air pollution co-exposures and pollutants aged under atmospheric irradiation, and targeting wider participant groups. The initial outcomes from the study resulting from this protocol will allow future work to focus on the areas of cognitive dysfunction identified.

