### 2.3. Participant Volunteers

This study will aim to recruit 45 clinically healthy individuals aged 50 and above with a family history of dementia. See Appendix A for full inclusion and exclusion criteria. Recruitment began in May 2023 and due to significant challenges, as explained in detail in the discussion section, the originally planned sample size was reduced to 15 participants. The study is currently ongoing, and data collection is expected to be completed by the end of 2023. See Table 1 for study timeline.

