#### 2.3.1. Power Calculation

Based on effect size and variance from a currently unpublished study [35] looking at cognitive load and attention (measured as change in response time (
Δ
RT) after Diesel Exhaust exposure (
Δ
RT = 22 ms, s.d. = 25 ms), a sample size of 30 subjects will have 90% power to detect significant response time changes of 15 ms assuming the standard significance level of *p* < 0.05. We acknowledge this current study is a different design utilising an older adult population and have, therefore, calculated for a slightly smaller effect size than that of the previous study to compensate for larger RT variance in older adults. As longitudinal studies are prone to extensive participant attrition, the sample size of 45 aims to allow full data to be collected for a minimum of 30 participants. Power calculations were performed using PS [36].

In response to recruitment challenges, we revised the sample size, prompting a re-exploration of the sample size estimate and power calculation to identify the minimum sample likely to yield valuable results. The proposed study design involves comparing the impact of four pollution exposures by examining the differences between pre- and post-exposure measurements relative to baseline measurements. The independent design from the previous study, featuring one measure per group, makes it unfeasible to extrapolate data. Therefore, under the assumption of a conservative correlation among repeated measures set at 0.5, a minimum sample size of 11 participants is needed to achieve 90% power in detecting a moderate (0.45) effect size at a significance level of 0.05.

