#### 2.3.3. Recruitment

Participants will be recruited from the general public. Volunteers who are employees of The University of Manchester or Manchester University NHS Foundation Trust will be permitted to take part if not involved with the project. Advertisement posters will be placed in public spaces including local community groups, places of worship, and NHS and university buildings. Social media advertisements will be run using official accounts of the University of Manchester, NHS Manchester Foundation Trust, and Research for the Future. We will also contact participants who have previously given permission to be contacted for research studies. Due to potential sex-dependent effects of aerosol exposure, we aim to collect equal numbers of biologically male and female participants.

To promote participant retention, participant payment will increase each visit so that there is an increasing incentive to continue participation as the study continues. Informal participant feedback will be collected each visit to improve subsequent visit comfort and amend the protocol as necessary. Data from those who discontinue participation, whether through personal withdrawal or change in eligibility, will be included in data analysis where inclusion of partial data is possible.

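### The revised target of 15 at the assumed 33% dropout gives 10 expected completers, one below the article's stated minimum of 11 (minor inconsistency)

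*Protocol article*

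**What the plan says.** Section 2.3.1 of the protocol article contains two sample-size statements. The first belongs to the original plan: "the sample size of 45 aims to allow full data to be collected for a minimum of 30 participants". The second follows the recruitment difficulties: "under the assumption of a conservative correlation among repeated measures set at 0.5", it concludes that "a minimum sample size of 11 participants is needed to achieve 90% power". The power named there is for "detecting a moderate (0.45) effect size at a significance level of 0.05". The comparison it has in mind is described as "comparing the impact of four pollution exposures by examining the differences between pre- and post-exposure measurements relative to baseline measurements".

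Section 2.3 reports that "the originally planned sample size was reduced to 15 participants". The Discussion explains that the team "adjusted the target to a smaller sample size of 15, assuming a similar dropout rate (33" per cent).

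Two other places matter. Section 2.3.3 says that data from people who discontinue "will be included in data analysis where inclusion of partial data is possible". Section 2.7 plans generalised estimating equations or random-effects models, with the choice depending on how much data are missing or partial.

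**The concern.** The minimum of 11 and the target of 15 are linked by the dropout assumption, and the article prints all three numbers. Applying the stated dropout to the stated target gives fewer people than the stated minimum. Nothing in the article reconciles them. A reader of section 2.3.1 would take it that the revised target supports 90% power with dropout allowed for; on the article's own figures it falls one participant short.

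This matters because the revised calculation is the article's quantitative support for continuing after the target was cut by two thirds. A number carrying that weight should agree with the other numbers it depends on.

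**Working it through.** **Inputs from the article**
- Revised recruitment target: 15 (section 2.3; Discussion)
- Assumed dropout: 33% (Discussion)
- Stated minimum: 11 for 90% power; effect size 0.45, correlation 0.5, significance level 0.05 (section 2.3.1)
- Original pair: 45 recruited for at least 30 with full data (section 2.3.1)

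**Inputs assumed**
- 0.45 is Cohen's f.
- There are four repeated measures, taken from the four pollution exposures named in section 2.3.1.

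**Step 1. Is 15 counted before or after dropout?** In the original plan, 30/45 = 2/3, a loss of 33.3%, so 45 is the number recruited and 30 the number with full data. The Discussion carries a similar loss over to 15. So 15 is also a number recruited.

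**Step 2. Expected completers.**
- Original: 45 × 2/3 = 30, which agrees with the article.
- Revised: 15 × (1 − 0.33) = 10.05, or 15 × 2/3 = 10, against a minimum of 11.
- Largest dropout that leaves 11 of 15: 4/15 = 26.7%.
- Recruits needed to expect 11 at 33% dropout: 11/0.67 = 16.4, so 17.

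**Step 3. Reproduce the stated 11.** Use the one-group within-subject F test with sphericity:
- noncentrality λ = f² × N × m/(1 − ρ)
- df1 = m − 1, df2 = (N − 1)(m − 1)

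With f = 0.45, ρ = 0.5 and m = 4, λ = 0.2025 × N × 4/0.5 = 1.62 N.

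| N | λ | df | Power |
|---|---|---|---|
| 10 | 16.20 | 3, 27 | 89.6% |
| 11 | 17.82 | 3, 30 | 92.8% |

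The smallest N with at least 90% power is 11, so the article's figure is reproduced exactly. At 10 the shortfall is 90 − 89.6 = 0.4 percentage points.

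**Step 4. Sensitivity to the assumed number of measures.**

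| Measures | Minimum N for 90% | Power at N = 10 |
|---|---|---|
| 3 | 12 | 82.5% |
| 4 | 11 | 89.6% |
| 5 | 9 | 94.0% |

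Of these, only four measures returns 11. A paired t test with a standardised difference of 0.45 would need 54, so that is not the calculation behind the stated figure. The count in step 2 uses none of these assumptions.

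**The case against.** The strongest reply is that the mismatch hardly matters. It is one participant, and 89.6% rounds to the stated 90%. That stands, and it is why the point is minor.

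Second, people who discontinue are not lost to the analysis. With five sequential exposures, someone who leaves part-way has still contributed, and sections 2.3.3 and 2.7 provide for partial data. Section 2.3.1 also says 11 participants, without calling them completers. Much of this stands: it would be wrong to say the plan leaves no margin. But the original calculation defined its 30 by full data, and the article does not use partial data to justify either 11 or 15. The printed numbers still disagree.

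Third, the Discussion already concedes reduced power and a higher risk of a Type II error, and claims only reasonable power for 15. That stands as a general disclosure. It does not tell the reader that the expected number falls below the stated minimum.

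Three stronger readings are tempting:
- A reader might infer that the revised trial is materially underpowered because of this slip. The documents do not support that. The loss against 90% is about 0.4 points on the reproducing calculation, and with five measures power at 10 would exceed 90%.
- A reader might want to size the lost participant with the earlier diesel study's response-time figures. Section 2.3.1 says that study cannot be extrapolated to the revised calculation, so those inputs bear on the choice of effect size and not on dropout.
- A reader might infer that 15 came from multiplying 11 by 1.33 (14.6, rounded up) instead of dividing by 0.67. The arithmetic fits, but the article does not say how 15 was reached.

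**Conclusion.** The inconsistency is real but minor. On the article's own target and dropout rate, 10 participants are expected to complete, against a stated minimum of 11. This follows from printed figures alone, given that 15 is a number recruited, which the 45-to-30 pair shows.

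The size in power terms is about 0.4 percentage points below the stated 90% (89.6% at 10, compared with 92.8% at 11). That percentage rests on reading 0.45 as Cohen's f, on four repeated measures and on sphericity. It also treats people who discontinue as contributing nothing, so partial data could narrow the gap. No endpoint, design feature or analysis choice turns on 10 rather than 11.

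**What to change.** Make section 2.3.1 and the Discussion agree on one completer number, in either of two ways:
- State that 15 recruits at 33% dropout give 10 expected completers, and quote the power at 10 together with the effect-size metric and number of measures used (89.6% if these are f and four).
- Keep 11 as the minimum, and state that it holds only if dropout is at most 4 of 15 (27%).

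If the team is relying on partial data to make up the difference, one clause saying so would help.

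The cost is about two sentences and a slightly less favourable stated figure. Recruiting 17 would also make the numbers agree at 33% dropout, but it is not required, and the article explains that recruitment was already the limiting factor.

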## 4. Administrative Information

### 4.1. Reporting Standards

The SPIRIT reporting guidelines were used to prepare this manuscript [61].

### 4.2. Trial Registration

Trial registered on ISRCTN registration number 85634746, accepted on 3 April 2023.

### 4.3. Protocol Version

Current protocol version 1.6, 23 February 2023.

### 4.5. Trial Status

The current protocol attached is version 1.6, dated 23rd February 2023. Recruitment began in May 2023 and the study is currently ongoing. It is expected that data analysis will begin in January 2024.

### 4.6. Dissemination

Our expectation is that after data analysis, information from this study will be widely disseminated in the medical and scientific community.

## Figures and Tables

**Figure 1 ijerph-21-00284-f001:**
[figure not shown]
Study data collection procedure. vs. = vital signs; nl = nasal lavage; sp = spirometry (lung function).

**Figure 2 ijerph-21-00284-f002:**
[figure not shown]
The two-way valve and mask set-up during exposure. Black arrows show airflow direction of one-way valves. Participants inhale air from the chamber (red line) and exhale into the surrounding room (dark grey line).

**Table 1 ijerph-21-00284-t001:** Study time schedule of enrolment, exposures, and visits. Exp = Exposure.

	Recruitment		Enrolment		Post-Enrolment						
			**First Wave (W1)**	**Second Wave (W2)**	**Exp 1 (W1)**	**Exp 2 (All)**	**Exp 3 (All)**	**Exp 1 (W2)**	**Exp 4 (All)**	**Exp 5 (All)**	**Remnant Exp(s)**
Start date		09-Jan-23	02-May-23	01-Jun-23	15-May-23	19-Jun-23	24-Jul-23	21-Aug-23	11-Sep-23	16-Oct-23	20-Nov-23
End date		30-Jun-23	31-May-23	30-Jun-23	02-Jun-23	07-Jul-23	11-Aug-23	25-Aug-23	29-Sep-23	03-Nov-23	30-Nov-23
ENROLMENT											
Information Sheet		X									
Informed Consent			X	X							
Eligibility Screen			X	X	X	X	X	X	X	X	X
VISITS											
Exp 1	Visit A				X			X			X
	Visit B				X			X			X
Exp 2	Visit A					X					X
	Visit B					X					X
Exp 3	Visit A						X				X
	Visit B						X				X
Exp 4	Visit A								X		X
	Visit B								X		X
Exp 5	Visit A									X	X
	Visit B									X	X
MEASURES											
Pre-Exposure					X	X	X	X	X	X	X
Post-Exposure					X	X	X	X	X	X	X

**Table 2 ijerph-21-00284-t002:** Summary of the cognitive tasks completed by participants pre and post exposure. Tasks will be administered in table order, starting with the Spatial *n*-back Task (SNB).

Task	Outcome Metrics	Cognitive Domain	Duration
Spatial *n*-back Task (SNB)	Working memory ability	Learning and memory	10 min
Face Identification Task (FIT)	Distractor suppression	Executive function	15 min
	Cognitive control		
Purdue Pegboard Test (PPT)	Gross movements of arms, hands, and fingers	Perceptual-motor function	10 min
	Fine motor extremity		
Expression Recognition Task (ERT)	Expression Discrimination	Socio-emotional cognition	15 min
	Approach bias		
Psychomotor Vigilance Task (PVT)	Sustained attention/vigilance	Attention	10 min
	Psychomotor speed		

## Data Availability

There are currently no plans to share participant-level datasets.

## Abbreviations

The following abbreviations are used in this manuscript:

eCRF	electronic case report form
ERT	Expression Recognition Task
FIT	Face Identification Task
GCP	good clinical practice
GPCog	general practitioner assessment of cognition
hCRF	hard-copy case report form
HRA	Health Research Authority
ICF	informed consent form
IRAS	Integrated Research Application System
MAC	Manchester Aerosol Chamber
MCRF	Manchester Clinical Research Facility
nl	nasal lavage
PI	principal investigator
PIS	participant information sheet
PM	particulate matter less than 2.5 micrometres in diameter
PPIE	Patient and Public Involvement and Engagement
PPT	Purdue Pegboard Test
PVT	Psychomotor Vigilance Task
RT	response time
SAE	serious adverse event
SDF	source data file
SNB	Spatial *n*-back Task
SOA	secondary organic aerosol
sp	spirometry
UREC	University of Manchester Research Ethics Committee
vs	vital signs

## Appendix A. Inclusion and Exclusion Criteria

The study inclusion criteria are:

- Age ≥ 50 years of age;
- Family history of dementia (first- or second-degree relative);
- Provision of signed, written, and dated informed consent, prior to any study specific procedures.

Participants will be excluded if any of the following criteria apply:

- Neurological or psychiatric disorder;
- General Practitioner Assessment of Cognition Score of ≤ 7;
- Current smoker (including e-cigarettes) or ex-smoker of less than 6 months abstinence, and < 20-pack/year history;
- Current pregnancy;
- Significantly abnormal spirometry;
- History of cardiac disease;
- History of chronic respiratory or airways disease;
- History of inflammatory diseases (e.g., rheumatoid arthritis, chronic periodontitis, inflammatory bowel disease);
- History of neurological or psychiatric disorders;
- History of organ transplant;
- Consumption of >3 units of alcohol in the 24 h preceding testing visit;
- Any vaccination in the week prior to the testing visit;
- Cold or flu in the 48 h prior to the testing visit;
- Visual impairment not correctable with glasses/contact lenses;
- Significant claustrophobia preventing the participant from wearing a mask over the nose and mouth for an hour;
- Concomitant medication use of neurologically active drugs such as opiates/ benzodiazepines/anti-epileptics, etc.;
- Substance misuse.

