### 2.6. Cognitive Measures

#### 2.6.1. Dementia Assessment

The General Practitioner Assessment of Cognition [57] (GPCog) is a screening tool for global cognitive impairment seen in those with dementia. The Participant Examination assessment (see Supplementary File S3) will be completed as part of eligibility screening. Briefly, participants are given a name and address to immediately repeat and remember. Participants are then asked to provide the exact day, complete two diagrams highlighting clock time, and tell the experimenter something that has happened in the news in the past week. Participants then recall the name and address they were asked to remember at the start. Usually, a score of 8 or below would involve additional information (Step 2: Informant Interview) from an informant, i.e., a family member who would know the participant and their current functioning compared to previous years. As we will not have access to an informant, participants will be allowed one error, so a score of 8 or 9 will indicate that participants are cognitively intact and can continue with the study.

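### The smoking exclusion in Appendix A uses a pack-year limit that points the wrong way: no reading of it makes a history of 20 or more a reason for exclusion

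*Protocol article*

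**What the plan says.** Section 2.3 of the protocol article sets out to "recruit 45 clinically healthy individuals aged 50 and above with a family history of dementia" and sends the reader to Appendix A for the full criteria. The second list in Appendix A opens with "Participants will be excluded if any of the following criteria apply", so one item is enough to exclude. The smoking item on that list reads "Current smoker (including e-cigarettes) or ex-smoker of less than 6 months abstinence, and < 20-pack/year history". No other part of the article gives a smoking or pack-year rule.

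Two other items on the list carry a numerical limit on a measured quantity: "General Practitioner Assessment of Cognition Score of ≤ 7" and "Consumption of >3 units of alcohol in the 24 h preceding testing visit". Section 2.3.5 has eligibility reviewed at the start of each visit and ends participation for anyone who no longer meets the criteria.

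**The concern.** On an exclusion list, a limit has to describe the people to be kept out. Here the cumulative-smoking limit describes those with the lighter history. A screener who applies the line as printed would not exclude anyone because of a heavy history, and might exclude people because theirs is light.

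Two things are at stake. First, this is a safety-related rule in a study of 60-minute inhaled exposures. Section 2.3.5 names short-term respiratory symptoms as the expected reactions and relies on screening to reduce that risk. Second, the line helps define who was studied. If its meaning depends on how a reader groups the words, the population cannot be stated, and the trial cannot be replicated or generalised with confidence.

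The unit adds to the difficulty. As printed it is a rate (packs per year), whereas cumulative exposure is measured in pack-years.

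**Working it through.** No sample-size, power or significance figure is involved, so this is a check of logic.

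**Inputs** (all from Appendix A unless noted)
- Meeting any one item excludes: "Participants will be excluded if any of the following criteria apply".
- The smoking item has three parts: current smoker (C); ex-smoker with under 6 months of abstinence (R, recent quitter); history below 20 (L). They are joined as C *or* R, *and* L.

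**Three ways to group the words**
- Reading A: (C or R) and L.
- Reading B: C or (R and L).
- Reading C: the *and* only separates list entries, so C, R and L each exclude.

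**Result for each type of volunteer, by this item alone**

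| Smoking status | History | Reading A | Reading B | Reading C |
|---|---|---|---|---|
| Never | 0 (below 20) | eligible | eligible | excluded |
| Current | below 20 | excluded | excluded | excluded |
| Current | 20 or more | **eligible** | excluded | excluded |
| Ex, under 6 months | below 20 | excluded | excluded | excluded |
| Ex, under 6 months | 20 or more | **eligible** | **eligible** | excluded |
| Ex, 6 months or more | below 20 | eligible | eligible | excluded |
| Ex, 6 months or more | 20 or more | **eligible** | **eligible** | **eligible** |

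Three facts follow.
1. Where someone with 20 or more is excluded (current smokers under B; current smokers and recent quitters under C), the reason is smoking status, never the amount smoked.
2. Wherever the history clause changes the outcome, the lighter history is excluded and the heavier one is not.
3. The last row is the same under all three readings: a long-abstinent ex-smoker with 20 or more passes.

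Under Reading C, one could take the word *history* to presuppose some smoking, which would spare never-smokers. The direction would not change: long-abstinent light ex-smokers would be excluded and long-abstinent heavy ones kept.

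**Comparison with the other limits.** The cognition item excludes 7 or below. This agrees with Section 2.6.1, where "a score of 8 or 9 will indicate that participants are cognitively intact and can continue with the study". The alcohol item excludes above 3 units. Both limits describe the people to be kept out; the pack-year limit alone does not.

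**Scale.** The article does not say how many volunteers have any smoking history. For orientation only, one participant is 1/15 = 6.7% of the revised target. The Discussion assumes 33% dropout, so 15 × (1 − 0.33) ≈ 10 would complete, and one participant is 1/10 = 10% of them.

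**The case against.** The strongest reply is that this is a drafting slip with little effect. The clause looks like an eligibility condition for ex-smokers (abstinent long enough and below the limit) of which only the abstinence half was turned round when it was moved to the exclusion list. Reading C would bar most healthy volunteers, so staff are unlikely to have applied it. The full protocol, version 1.6, is not shown, and the error may exist only in the article's appendix. All of this is plausible, but it is inference: nothing in the article states the intended rule, and Appendix A is where the reader is sent for the complete criteria.

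Other safeguards also count. Appendix A separately excludes abnormal spirometry and cardiac, chronic respiratory and inflammatory disease, and eligibility is rechecked at each visit. These would remove some heavy smokers. They would not remove one with normal spirometry and no diagnosis.

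A reader might infer four stronger points that the article does not support.
- *Heavier smokers in general stay eligible.* Current smokers with 20 or more do so only under Reading A; Reading B excludes all current smokers.
- *The line contradicts the clinically healthy population.* A long-abstinent ex-smoker without disease can be clinically healthy.
- *Smokers would add noise to every marker.* Each person is measured before and after all five exposures, so a stable shift from past smoking largely cancels in the contrast with clean air. Only a different response to exposure, or greater visit-to-visit variation, would matter, and the article gives no basis for sizing either.
- *The wrong people were enrolled.* Nothing shows that any affected person was.

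**Conclusion.** The criterion is wrong as written, and that holds under every grouping of its words. It rests only on the item's place in the exclusion list and the direction of its inequality, not on any guess about intent. Who is wrongly kept in or out does depend on the reading. The one constant is that long-abstinent ex-smokers with 20 or more are never excluded by this item.

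The consequence is moderate: a safety-related eligibility rule that does not do what it appears meant to do, and a population that cannot be defined from the text. The other health exclusions and the within-person comparisons limit the harm. No endpoint, sample-size or power figure is affected, and the number of people concerned cannot be derived from the article. It should be corrected, but it is not a threat to the primary analysis.

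**What to change.** - Reconcile the line with the full protocol and the screening form, and state which rule was actually applied.
- Write smoking status and cumulative history as separate, unambiguous conditions. The sponsor should confirm the limit, its direction, and whether it covers all volunteers or only ex-smokers. No threshold is proposed here.
- Give the unit as pack-years.
- Check everyone enrolled against the confirmed rule and report any who fall outside it.
- Report smoking status and pack-years in the baseline table.

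The cost is one line in Appendix A, a matching line on the screening form if that carries the same wording, and a short check of about 15 records. Table 1 has enrolment ending in June 2023, before the article appeared in February 2024, so the change is mainly a correction of the record plus that check; both remain possible after recruitment.
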